# Comparison of the effects of neostigmine and sugammadex on postoperative residual curarization and postoperative pulmonary complications by means of diaphragm and lung ultrasonography: a study protocol for prospective double-blind randomized controlled trial

**DOI:** 10.1186/s13063-022-06328-3

**Published:** 2022-05-07

**Keywords:** Diaphragm ultrasonography, Lung ultrasound, Postoperative pulmonary complications, Postoperative residual curarization

## Abstract

**Background:**

Postoperative residual curarization (PORC) may be a potential risk factor of postoperative pulmonary complications (PPCs), and both of them will lead to adverse consequences on surgical patient recovery. The train-of-four ratio (TOFr) which is detected by acceleromyography of the adductor pollicis is thought as the gold standard for the measurement of PORC. However, diaphragm function recovery may differ from that of the peripheral muscles. Recent studies suggested that diaphragm ultrasonography may be useful to reveal the diaphragm function recovery, and similarly, lung ultrasound was reported for the assessment of PPCs in recent years as well. Sugammadex reversal of neuromuscular blockade is rapid and complete, and there appear to be fewer postoperative complications than with neostigmine. This study aims to compare the effects of neostigmine and sugammadex, on PORC and PPCs employing diaphragm and lung ultrasonography, respectively.

**Methods/design:**

In this prospective, double-blind, randomized controlled trial, patients of the American Society of Anesthesiologists Physical Status I–III, aged over 60, will be enrolled. They will be scheduled to undergo arthroplasty under general anesthesia. All patients will be allocated randomly into two groups, group NEO (neostigmine) and group SUG (sugammadex), using these two drugs for reversing rocuronium. The primary outcome of the study is the incidence of PPCs in the NEO and SUG groups. The secondary outcomes are the evaluation of diaphragm ultrasonography and lung ultrasound, performed by an independent sonographer before anesthesia, and at 10 min and 30 min after extubation in the post-anesthesia care unit, respectively.

**Discussion:**

Elimination of PORC is a priority at the emergence of anesthesia, and it may be associated with reducing postoperative complications like PPCs. Sugammadex was reported to be superior to reverse neuromuscular blockade than neostigmine. Theoretically, complete recovery of neuromuscular function should be indicated by TOFr > 0.9. However, the diaphragm function recovery may not be the same matter, which probably harms pulmonary function. The hypothesis will be proposed that sugammadex is more beneficial than neostigmine to reduce the incidence of PPCs and strongly favorable for the recovery of diaphragm function in our study setting.

**Trial registration:**

ClinicalTrials.gov NCT05040490. Registered on 3 September 2021

**Supplementary Information:**

The online version contains supplementary material available at 10.1186/s13063-022-06328-3.

## Background

Neuromuscular blocking agents (NMBAs) which provide muscle relaxation effects may play an important role in balanced general anesthesia. It could facilitate endotracheal intubation and improve surgical condition. At the end of the surgery, neuromuscular blocking agents are recommended to be reversed completely before tracheal extubation. However, the incidence of postoperative residual curarization (PORC) was reported as high as 57.8% at the time of tracheal extubation and 45.2% in the post-anesthesia care unit (PACU) [1]. Although the use of reversal agents and neuromuscular monitoring has also been recommended, it is conceivable that the situation is far from adequate. Some published surveys documented that only 35% of anesthesiologists thought that quantitative neuromuscular monitoring is necessary [2], and only 17% of them chose to use it [3]. A recent study has shown that nearly 50% of patients did not receive a reversal of neuromuscular block, either neostigmine or sugammadex [4].

Subjective or objective monitors of the neuromuscular block are advocated in clinical practice, of which acceleromyography monitor is the most commonly used to assess neuromuscular block quantitatively in real time. It adopts the train-of-four (TOF) stimulation pattern and displays the TOF ratio (TOFr, T4/T1), which could help the clinician to identify residual muscle blockade by the cutoff value of TOFr < 0.9 [5]. However, the TOF monitoring technique was not routinely carried out in the operating room scenario [6], because these devices require initialization and baseline calibration, and the electrode placement sites sometimes will be interrupted when the patient’s arms are tucked under surgical drapes along the body. Moreover, TOF stimulation may bring unpleasant experiences to patients when they are awake.

Ultrasonography is considered a non-invasive, visualized technique to assist in more and more decision-making for anesthesiologists and intensive care unit (ICU) clinicians. Diaphragm ultrasound has been paid close attention to assess respiratory function, for the diaphragm is the principle respiratory muscle that contributes to more than 60% of tidal volume in every breath [7]. In recent years, several pilot studies have demonstrated that diaphragm ultrasound could be used for the detection of residual muscle dysfunction [8–10]. Our preliminary study also suggested that diaphragmatic excursion (DE) and thickening fraction (TF) during deep breathing have potential efficacy for detecting PORC and were significantly correlated with TOFr in non-thoracic and non-abdominal surgery patients [11]. These results proved that diaphragm ultrasound could provide a feasible measurement to recognize PORC since it is more convenient and comfortable for patients than acceleromyography.

Acetylcholinesterase inhibitors (AChEI) such as neostigmine are commonly administrated to reverse the neuromuscular block effect, which has been considered the gold standard in clinical settings. However, neostigmine has some unavoidable side effects such as bradycardia, cholinergic crisis, and hyperresponsiveness of the bronchus [12]. Moreover, neostigmine may be ineffective for reversing deep neuromuscular block, which may be prone to increase the occurrence of PORC in some circumstances. Some evidence showed that a large dose of neostigmine may lead to transient muscle weakness [13].

Evidence from many retrospective and observational cohort studies have suggested that PORC are associated with many adverse consequences which may contribute to postoperative pulmonary complications (PPCs) [14, 15]. Residual paralysis can cause weakness of the ventilatory muscles, inability to cough, dysfunction of upper airway patency, and impaired swallowing reflex, to increase the risk of hypoxemia, atelectasis, aspiration pneumonia, airway obstruction, and other postoperative pulmonary complications [16, 17]. Therefore, it has been suggested that reducing PORC may decrease the incidence of PPCs. PPCs are harmful and related to poor patient outcomes, especially in high-risk patients, such as elderly patients. The incidence of PPCs was reported to reach 48.3% in elderly patients after administrating neostigmine or without any antagonists [18]. Early and rapid diagnosis is crucial for subsequent treatment. Although thoracic computed tomography (CT) is considered the gold standard of diagnosing PPCs, limitations such as radiation exposure hazards and inconvenient transfer for critical illness patients make it difficult to be routinely performed. Multiple investigations have the evidence that lung ultrasound (LUS) can outperform CT in portability and convenience, and it has been validated as an alternative tool for assisting in detecting atelectasis, pulmonary effusion, and pneumonia, etc. [19, 20].

Sugammadex, the first γ-cyclodextrin drug, is a specific antagonist for neuromuscular block induced by rocuronium. It has been proved by many studies that sugammadex can give a rapid, complete, and long-lasting recovery of muscle strength [21–23]. Compared to neostigmine, sugammadex can minimize the occurrence of PORC and may have the potential to lower the incidence of PPCs [15, 24].

In this prospective double-blinded randomized study, we hypothesize that the incidence of PPCs is lower after reversal with sugammadex than with neostigmine. Considering the incidence of PORC, we postulate that it is lower after reversal with sugammadex than with neostigmine through diaphragm ultrasound. Although the lung ultrasound could not be a substitute for thoracic CT in discerning PPCs, we try to evaluate the difference of changes in lung ultrasound after reversal of neuromuscular block by sugammadex and neostigmine respectively.

## Methods/design

### Study aim

This trial aims to compare the incidence of PORC and PPCs in the sugammadex and neostigmine groups utilizing diaphragm ultrasonography and lung ultrasound and try to conclude whether sugammadex has an advantage over neostigmine in eliminating the occurrence of PORC and PPCs.

### Study design/setting

This planned study is a prospective, double-blind, randomized controlled trial of superiority, undertaken in Peking Union Medical College Hospital; Fig. 1 is the trial flow chart, and Fig. 2 is the study timeline. The study has been approved by the Ethics Committee of Peking Union Medical College Hospital (No. JS-2674) and has been prospectively registered at ClinicalTrials.gov, NCT05040490, as “Comparison of the Effects of Neostigmine and Sugammadex on Postoperative Residual Curarization and Postoperative Pulmonary Complications Detected by Diaphragm and Lung Ultrasonography” on 3 September 2021. All patients enrolled must sign the patient consent form (see Additional file 1). We used the Standard Protocol Items: Recommendations for International Trials (SPIRIT) reporting guidelines [25], and Additional file 2 is the SPIRIT checklist.

**Fig. 1 Fig1:**
[figure not shown]
Study flow chart. *t*_1_, preanesthetic period; *t*_2_, induction of anesthesia; *t*_3_, end of surgery; *t*_4_, extubation; *t*_5_, 10 min after extubation; *t*_6_, 30 min after extubation; POD30, postoperative day 30; PPCs, postoperative pulmonary complications

**Fig. 2 Fig2:**
[figure not shown]
Study timeline. *t*_1_, preanesthetic period; *t*_2_, induction of anesthesia; *t*_3_, end of surgery; *t*_4_, extubation; *t*_5_, 10 min after extubation; *t*_6_, 30 min after extubation; POD30, postoperative day 30; PPCs, postoperative pulmonary complications

### Participants

Elderly patients are more vulnerable to PPCs, and the incidence of PPCs in patients over 60 years was 19.2% [26]. To facilitate TOF monitoring on the upper limb and enlist relatively older patients, we plan to enroll in total of 414 participants undergoing arthroplasty surgery under general anesthesia, according to the calculation of sample size.

#### Inclusion criteria

The following are the inclusion criteria:American Society of Anesthesiologists (ASA) Physical Status I–IIIAged over 60 yearsAnesthesia induction with rocuronium as NMBAs, maintenance with volatile sevofluraneScheduled to undertake arthroplasty surgerySigned the informed consent form

#### Exclusion criteria

The following are the exclusion criteria:Those with a history of hepatic or renal disease, chronic or acute alcoholism, allergy or hypersensitivity to sugammadex or neostigmine, current medication with effects on the central nervous system, and a history of dysfunction of the neuromuscular system.Those with diaphragm insufficiency (which can be determined by maximal inspiratory pressures and phrenic nerve stimulation) or massive pleural effusion.Those undergoing upper abdominal laparotomy will be excluded, after which we cannot obtain a satisfactory ultrasound imaging or do not have space for placement of the ultrasonic probe.Those who are extremely old and frail (which can be determined by the FRAIL Scale) and need adjustment of drug dosage.

### Randomization, allocation, and concealment

Once informed consent has been received and the preoperative assessment completed by major anesthetists the day before surgery, patients will be entered into the trial. The randomization procedure will be website-based using random blocks and stratified by the reversal drug the subject takes, which will be done by an independent anesthetist other than major anesthetists. That is, subjects will be randomly allocated to either the sugammadex (SUG) group or the neostigmine (NEO) group in a variable block randomization method, ensuring a 1:1 equal distribution of patients into each group. For allocation concealment, table assignment to the SUG group or the NEO group and drug preparation will be managed by a pharmacist with limited involvement in major anesthesia procedures. Besides, diaphragm ultrasound and LUS will be performed by a skilled sonographer (an independent anesthesiologist) not involved in patient care. Lastly, patients and major anesthetists are both blinded to the treatment assignment.

The randomization codes shall be sealed in duplicate and kept in envelopes by the project leader (PI). Both unblinding is performed by PI who preserved randomization codes. After the data has been blinded and determined to be reliable, the first unblinding will be carried out, only listing the group to which each patient belongs (group A or B). The second unblinding will be performed after the end of the statistical analysis, determining the SUG or NEO group. In this double-blind study, an emergency letter will be attached to every randomization code, illustrating the group and medication of the subject. Emergency letters shall be sealed and kept by PI, and shall not be opened unless there is an emergency and it is necessary to know the medication he/she has received. Once opened, the trial of this patient will be discontinued, and the reason shall be documented in the case report form (CRF).

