### Intervention

Patients who meet the enrollment criteria will be randomized 1:1 to either the NEO or the SUG group, receiving NEO or SUG as reversal drugs, respectively, in identical volumes and injectors, with other treatments exactly the same. Patients in the NEO group will receive 50 μg kg^−1^ neostigmine and 15 μg kg^−1^ atropine, while those in the SUG group will receive 2 mg·kg^−1^ sugammadex before the end of operation when TOF count (TOFc) ≥ 2. Drug dosing of anesthesia induction, anesthesia maintenance, and reversal will all be dependent on ideal body weight.

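### The article names the randomised drug as the stratification factor; this is most likely a misstatement, to be deleted or replaced by the factor actually used, with the primary analysis adjusted for ASA class and age

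*Protocol article*

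**What the plan says.** The section on randomization, allocation and concealment of the protocol article states that the procedure runs through a website, uses random blocks and is "stratified by the reversal drug the subject takes". Its next sentence is worded as an explanation of the first. It says that subjects are allocated at random to sugammadex or neostigmine "in a variable block randomization method, ensuring a 1:1 equal distribution of patients into each group". No baseline factor is named there or elsewhere in the article.

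The Intervention section says that eligible patients "will be randomized 1:1 to either the NEO or the SUG group, receiving NEO or SUG as reversal drugs". The abstract defines the two groups in the same way, by the drug used to reverse rocuronium.

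For the analysis, the Statistical analyses section gives a chi-squared test for dichotomous data, and the primary outcome, the incidence of postoperative pulmonary complications (PPCs) over 30 days, is dichotomous. No covariate adjustment is mentioned. The section headed Other parameters lists ASA physical status and an item called year, which I read as age.

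**The concern.** A stratification factor has to be known when the patient is randomised, and each stratum has to be able to hold both arms. The reversal drug meets neither condition. The stated rule is therefore wrong as a description of the procedure, and a reader cannot tell from that clause whether the list was unstratified or used a baseline factor that has been misnamed.

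The difference matters for the analysis. If there was no stratification, the clause is noise. If there was a real factor, the primary comparison should take account of it, and the chi-squared test does not. Recruitment was in progress at publication, so an uncorrected clause is also likely to be carried into the results report.

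**Working it through.** **1. Is the named factor available at randomisation?** The sequence in the article is:

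| Step | When | Source |
|---|---|---|
| Entry into the trial | After consent and assessment: "the preoperative assessment completed by major anesthetists the day before surgery, patients will be entered into the trial" | Randomization section |
| Reversal drug given | "before the end of operation when TOF count (TOFc) ≥ 2" | Intervention section |

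The drug is given after entry, and which drug it is follows from the allocation. It is not a baseline characteristic.

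**2. Can 1:1 allocation hold within such strata?** Define stratum S as all patients taking sugammadex. Every patient in S is in the SUG group, so the ratio within S is 1:0. The other stratum is 0:1. A 1:1 block within either is a contradiction. Read literally, the clause conflicts with the 1:1 ratio stated in the next sentence and in the Intervention section.

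**3. Is there a workable scheme once the clause is removed?** Yes. What remains is website-based random allocation, 1:1, in blocks of varying size, run by an independent anesthetist, with assignment and drug preparation handled by a pharmacist. That is a complete unstratified scheme.

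**4. Does the sample size depend on the clause?** No, but the plan's figure is reproduced here because the event counts below use the same rates. The article gives 15.4% as the rate used and mentions 5% for non-cardiac surgery in general. It does not label 5% as the sugammadex rate, so that is an assumption. With two-sided alpha 0.05 (sidedness also assumed), 90% power and unpooled variance:

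n = (1.960 + 1.282)² × (0.154 × 0.846 + 0.05 × 0.95) / (0.154 − 0.05)² = 172.7 per group

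172.7 × 1.2 = 207.3, which matches the stated 207. Removing the clause changes none of these inputs.

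**5. How many primary events are expected?** Events = n per arm × (sum of the two rates).

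- 15.4% v 5%: 165 × 0.204 = 33.7 (about 20% lost from 207); 207 × 0.204 = 42.2.
- The Discussion cites an observational cohort with a 30–50% reduction. That gives sugammadex rates of 0.154 × 0.7 = 10.8% and 0.154 × 0.5 = 7.7%. At 207 per arm the events are 207 × (0.154 + 0.108) = 54 and 207 × (0.154 + 0.077) = 48.

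**6. How much could chance imbalance in ASA class move the result without strata?** The article gives no ASA distribution and no risk by class. For illustration, assume that 30% of patients are ASA III, with a PPC risk 10 points higher than the others.

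- SD of the between-arm difference in the ASA III proportion: √(2 × 0.3 × 0.7 / 207) = 4.5 points.
- A 2-SD imbalance is 9 points, or 0.09 × 207 ≈ 19 patients.
- Shift in the risk difference: 0.09 × 0.10 = 0.9 points, or 0.009 × 207 ≈ 2 events.
- An imbalance of 5 patients: 5 × 0.10 = 0.5 event.
- With a 20-point excess risk these double: 1.8 points, about 4 events, and 1 event for 5 patients.

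The difference implied by 15.4% v 5% is 10.4 points.

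**The case against.** The strongest defence is that the article corrects itself at once. The sentence after the clause restates the procedure as plain 1:1 variable-block randomisation, and the abstract and the Intervention section agree with it. The natural reading is that the word for stratified was used loosely to mean divided into groups by drug. That defence stands as regards the validity of allocation. It does not make the clause correct, and it does not exclude a real factor under the wrong name.

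The second defence is that stratifying on prognostic factors is optional. The article never claims to balance ASA class, age or joint, and unstratified blocks at about 207 per arm are acceptable. This also stands: the absence of prognostic strata is not a defect here.

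Three stronger readings are tempting, and the document supports none of them.

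- A reader might infer that the arm was known before the patient was randomised. Nothing else in the article points that way, and the described separation of roles points against it.
- A reader might infer that the procedure cannot be carried out. The clause cannot, but the scheme in the following sentence can.
- A reader might infer that, with so few events, a few unbalanced high-risk patients would move a large part of the result. Expected event counts alone do not show this. Under the illustrative assumptions, 5 patients move half an event to one event, and a 2-SD imbalance moves 0.9 to 1.8 points against 10.4.

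**Conclusion.** The clause is wrong as written: the randomised treatment cannot be a stratification factor. This follows from the article's own definition of the groups and needs no assumption. It is most likely a wording error. It does not show that allocation is invalid, and it leaves the sample size untouched.

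What the article leaves open is whether the website list used any baseline factor, which only the list itself can answer. Covariate adjustment does not depend on that answer, because ASA class and (on my reading of the item called year) age are collected anyway. Adjustment is recommended as a cheap protection against chance imbalance and a possible gain in precision, not because a bias has been shown. The imbalance figures rest on an assumed 30% ASA III and an assumed excess risk of 10 to 20 points; the event counts rest on the unlabelled 5%, or on 7.7–10.8% from the cited reduction.

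**What to change.** 1. Check the website list. If it used no baseline factor, delete the clause so that the text describes unstratified 1:1 allocation in variable blocks. If it did use one, name it in place of the drug and include it in the primary analysis. State which applied to patients already randomised.
2. Do not add new strata during recruitment. That would create two randomisation regimes in one trial.
3. In either case, make the primary analysis of PPC incidence a logistic regression on group, ASA class and age. Report the risk difference standardised over the trial population, with its confidence interval. Keep the chi-squared test as a supporting analysis. Confirm that the item called year is age, and fix the coding of both covariates before the first unblinding.

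The cost is a one-sentence correction and slightly more analysis work. With ASA class coded as I–II v III and age as linear, the model has three coefficients besides the intercept. At the lowest count above, that is 33.7 / 3 ≈ 11 events per coefficient. No new data and no change to the number of patients are needed.

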### Outcomes

#### Primary endpoint

The primary outcome will be the incidence of PPCs 30 days after surgery in neostigmine and sugammadex groups. Using conventional broad criteria for diagnosis of PPCs, any postoperative pulmonary abnormality that adversely affects the clinical course of a patient could be defined as a PPC, including acute respiratory distress syndrome (ARDS), atelectasis, bronchospasm, pleural effusion, pneumothorax, respiratory failure, respiratory infection, and various other forms of upper airway obstruction [33–35] (see Table 1 for more details of its definition). The PI will make a phone call on postoperative day 30 (POD30) to retrospectively check whether there have been PPCs after the surgery till now and make a detailed record of the symptoms, severity, and kind of PPCs on the CRFs.

**Table 1 Tab1:** Definition of postoperative pulmonary complications (PPCs) [36]

PPCs	Definition
**Acute respiratory distress syndrome (ARDS)**	Acute onset of hypoxemia (partial pressure of oxygen, arterial (PaO_2_)/fraction of inspired oxygen (FiO_2_) ≤ 300 mmHg) with new bilateral infiltrates in the setting of either a normal pulmonary arterial wedge pressure (PAWP ≤ 18 mmHg) or the absence of suspected of left atrial hypertension when PAWP was not available
**Atelectasis**	Collapse of the alveoli; lung opacification with a shift of the mediastinum, hilum, or hemidiaphragm toward the affected area; and compensatory over inflation in the adjacent non-atelectatic lung
**Bronchospasm**	Newly detected expiratory wheeze treated with bronchodilators
**Pleural effusion**	Chest radiograph demonstrating blunting of the costophrenic angle, evidence of displacement of adjacent anatomical structures, or (in supine position) a hazy opacity in one hemithorax with preserved vascular shadows
**Pneumothorax**	A collection of air in the pleural space (the area with no vascular bed surrounding the visceral pleura)
**Respiratory failure**	Postoperative PaO_2_ 60 mmHg on room air, a PaO_2_/FiO_2_ < 300 mmHg, or arterial oxyhemoglobin saturation measured with pulse oximetry < 90% and requiring oxygen therapy
**Respiratory infection**	Treatment with antibiotics for a respiratory infection, plus at least one of the following criteria: new or changed sputum, new or changed lung opacities, fever, and leukocyte count > 12,000/mm^3^

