### Statistics

#### Data management and monitoring

Data will be collected using a CRF, and all data from the CRFs will be checked by two investigators before being transferred into an Excel workbook. The digital ultrasound image/video will be copied from the ultrasound machine and stored in a mobile hard disk for review. All data will be kept by the PI independently during and after the trial. An independent Data and Safety Monitoring Committee will oversee the study conduct, report the adverse events, review the quality of collected data, and analyze the fidelity of the study to the protocol on a semiannual basis. The committee consists of a surgeon, an ICU physician, and an anesthesiologist not involved in the study. Also, the Ethics Committee of Peking Union Medical College Hospital will play a role in it. For patients who discontinue or deviate from the protocol, the data of whom will be discarded and that of a new legitimate patient will be recorded for substitution.

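### The project leader both keeps the sealed allocation codes and makes the day-30 call that records the primary outcome, an avoidable risk of detection bias

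*Protocol article*

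**What the plan says.** Under Randomization, allocation, and concealment, the protocol article makes the PI custodian of the codes ("The randomization codes shall be sealed in duplicate and kept in envelopes by the project leader (PI") and of the emergency letters: "Emergency letters shall be sealed and kept by PI, and shall not be opened unless there is an emergency". The letters reveal treatment patient by patient: "an emergency letter will be attached to every randomization code, illustrating the group and medication of the subject". The PI also carries out the planned unblinding: "Both unblinding is performed by PI who preserved randomization codes". The first step gives group A or B only and is timed as follows: "After the data has been blinded and determined to be reliable, the first unblinding will be carried out". Which group is sugammadex is revealed only once the analysis is finished.

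Under Primary endpoint, the primary outcome is obtained so: "The PI will make a phone call on postoperative day 30 (POD30) to retrospectively check whether there have been PPCs". The PI also writes the symptoms, severity and kind of complication on the case report form (CRF).

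On who is blinded, the randomization section says: "Lastly, patients and major anesthetists are both blinded to the treatment assignment". Statistical analyses adds a blinded statistician. The ultrasound examinations have an independent sonographer. No blinded assessor is named for PPCs. Data management and monitoring adds: "All data will be kept by the PI independently during and after the trial".

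**The concern.** Blinding of outcome assessment is strongest when the assessor has no means of learning the allocation. Here the assessor of the primary outcome is the person holding every means of learning it. This is not a detail left to a fuller document, since the article itself assigns both duties to the same role. It gives the ultrasound measurements an independent examiner but does not do the same for the primary endpoint.

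The endpoint leaves room for this to matter. A retrospective call has to turn a patient's recollection into a yes or no under a broad definition that admits any pulmonary abnormality affecting the clinical course. If the caller knew or guessed the arm, more probing or readier classification in one arm would create a difference between arms that no later analysis could remove. The trial's stated hypothesis favours sugammadex, so the direction of such an error is easy to imagine.

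**Working it through.** **Roles set side by side (protocol article)**

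| Duty | Held by | Section |
|---|---|---|
| Randomization procedure | independent anesthetist | Randomization, allocation, and concealment |
| Assignment table, drug preparation | pharmacist | same |
| Custody of sealed codes | PI | same |
| Custody of sealed emergency letters | PI | same |
| Both unblinding steps | PI | same |
| Day-30 call and PPC record | PI | Primary endpoint |
| Custody of all data | PI | Data management and monitoring |
| Named as blinded | patients, major anesthetists | Randomization, allocation, and concealment |
| Named as blinded | statistician | Statistical analyses |

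The PI appears on both sides, as code holder and as primary assessor, and is absent from the blinded roles. A pharmacist with no described outcome role already handles the assignment table.

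**Emergency openings.** Because the PI keeps the letters, an emergency opening involves the PI. The patient is then discontinued, and Data management and monitoring discards and replaces the data of such patients. That patient's call would therefore not reach the analysis, but the code holder then has a part in who stays in it.

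**Illustration of what is at stake.** The document gives no figure for biased recording, so the recording fractions below are assumptions.

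- Inputs from Sample size calculation: 15.4% incidence, 207 per arm including a 20% loss allowance. Evaluable after that loss: 207 × 0.8 = 165.6, about 166.
- Assumed: no true difference; 90% of neostigmine events recorded, and a fraction r of sugammadex events.
- Recorded rates: p1 = 0.154 × 0.90 = 0.1386; p2 = 0.154 × r.
- Test: uncorrected χ² = (x1/n − x2/n)² / [2p̄(1 − p̄)/n], with p̄ = (x1 + x2)/(2n); significant if above 3.841.
- False-positive rate: the sum of Bin(x1; n, p1) × Bin(x2; n, p2) over all significant pairs (x1, x2).

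| r | p2 | Expected recorded events at 207 (NEO vs SUG) | False-positive rate, 207 per arm | False-positive rate, 166 per arm |
|---|---|---|---|---|
| 90% | 0.1386 | 28.7 vs 28.7 | 4.9% | 5.0% |
| 85% | 0.1309 | 28.7 vs 27.1 | 5.5% | 5.5% |
| 80% | 0.1232 | 28.7 vs 25.5 | 7.4% | 7.0% |
| 70% | 0.1078 | 28.7 vs 22.3 | 15.7% | about 14% |
| 60% | 0.0924 | 28.7 vs 19.1 | 31% | about 26% |

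Check of the 70% row by normal approximation at 207 per arm: p̄ = (0.1386 + 0.1078)/2 = 0.1232; standard error under the null √(2 × 0.1232 × 0.8768/207) = 0.0323, and nearly the same under the alternative; difference 0.0308. The upper tail starts at (1.96 × 0.0323 − 0.0308)/0.0323 = 1.01, probability about 0.157; the lower tail adds about 0.002. The total of about 0.159 agrees with the exact 15.7%.

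A gap of 5 or 10 percentage points in recording does little. Inflation becomes serious only at gaps of 20 points or more, about 6 or more recorded events at 207 per arm.

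**The case against.** A reader might infer that the primary assessor is unblinded, or that the double-blind claim fails for the person who decides the result. The document does not support that. Codes and letters are sealed, and letters are for emergencies only. The day-30 records belong to the data that must be judged reliable before even the A/B split is released, so on the plan's own timetable the calls come before either unblinding. The PI is not described as generating the sequence or preparing drug, and custody of the data is no evidence of knowing the allocation. On the plan as written, learning an allocation outside an emergency means breaking a seal against the protocol. All of this stands, and it limits the point to a risk.

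A reader might also infer that the endpoint is purely subjective and rests on one unchecked person. Table 1 ties several PPCs to findings made outside the call: blood gases, radiographs, oxygen saturation, antibiotic treatment, leukocyte count. Two investigators check the CRFs, an independent committee reviews data quality twice a year, and the article does not say that the call is the only source of PPC data. This stands in part. Neither check is described as blinded adjudication, the catch-all wording and patient recall leave room for judgement, and the call is the only 30-day ascertainment procedure described.

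Finally, the larger false-positive rates need the caller to know or guess the arm and to miss many more events in one arm. That is correct. They show sensitivity and do not predict bias.

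**Conclusion.** The point holds as an avoidable weakness in the separation of duties. One role holds the allocation and records the primary outcome, that role is not named as blinded, and the only safeguard described between the two duties is a seal in that role's own keeping. It is not an established failure of the blind.

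The false-positive rate runs from close to nominal to about 31% at 207 per arm, or about 26% at 166, depending entirely on recording fractions that the document neither gives nor suggests. No sample size, endpoint or test changes. The point should be fixed because the remedy is cheap and biased ascertainment cannot be repaired at analysis; it does not by itself invalidate the trial.

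**What to change.** Either of two changes would do:

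1. Transfer the codes, the emergency letters and both unblinding steps to the pharmacist who already manages the assignment table and has no outcome role.
2. Leave custody with the PI, and have the day-30 call and the PPC classification done from a fixed script by an existing investigator with no access to codes or letters.

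In both cases, state in the protocol that the PPC assessor is blinded to allocation until the analysis is complete.

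The cost is a small reassignment of existing roles and a short amendment. Under the first option the amendment must also say who is reached for emergency unblinding. Trial status says that recruitment was under way, so the change protects only the calls still to be made; the report should state how many were made under the earlier arrangement.
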